# The impact of the Trauma Triage App on pre-hospital trauma triage: design and protocol of the stepped-wedge, cluster-randomized TESLA trial

**DOI:** 10.1186/s41512-020-00076-1

**Published:** 2020-06-18

**Keywords:** Triage, Trauma Triage App, Prediction model, Emergency Medical Services, Ambulance, Impact, Trial, Stepped-wedge, Cluster-randomized, Unidirectional crossover

## Abstract

**Background:**

Field triage of trauma patients is crucial to get the right patient to the right hospital within a particular time frame. Minimization of undertriage, overtriage, and interhospital transfer rates could substantially reduce mortality rates, life-long disabilities, and costs. Identification of patients in need of specialized trauma care is predominantly based on the judgment of Emergency Medical Services professionals and a pre-hospital triage protocol. The Trauma Triage App is a smartphone application that includes a prediction model to aid Emergency Medical Services professionals in the identification of patients in need of specialized trauma care. The aim of this trial is to assess the impact of this new digital approach to field triage on the primary endpoint undertriage.

**Methods:**

The Trauma triage using Supervised Learning Algorithms (TESLA) trial is a stepped-wedge cluster-randomized controlled trial with eight clusters defined as Emergency Medical Services regions. These clusters are an integral part of five inclusive trauma regions. Injured patients, evaluated on-scene by an Emergency Medical Services professional, suspected of moderate to severe injuries, will be assessed for eligibility. This unidirectional crossover trial will start with a baseline period in which the default pre-hospital triage protocol is used, after which all clusters gradually implement the Trauma Triage App as an add-on to the existing triage protocol. The primary endpoint is undertriage on patient and cluster level and is defined as the transportation of a severely injured patient (Injury Severity Score ≥ 16) to a lower-level trauma center. Secondary endpoints include overtriage, hospital resource use, and a cost-utility analysis.

**Discussion:**

The TESLA trial will assess the impact of the Trauma Triage App in clinical practice. This novel approach to field triage will give new and previously undiscovered insights into several isolated components of the diagnostic strategy to get the right trauma patient to the right hospital. The stepped-wedge design allows for within and between cluster comparisons.

**Trial registration:**

Netherlands Trial Register, NTR7243. Registered 30 May 2018, https://www.trialregister.nl/trial/7038.

## Background

Pre-hospital trauma triage is crucial to match an injured patient to the optimal definitive care facility [1]. Erroneously transporting a patient requiring specialized trauma care to a lower-level trauma center could lead to a delay in definitive care and is associated with higher mortality and morbidity rates [2]. Conversely, transporting a patient not in need of specialized trauma care to a higher-level trauma center results in extra costs and overutilization of resources [3]. These key metrics to evaluate the quality of field triage in trauma systems are termed undertriage and overtriage, respectively [1]. The Dutch National Health Care Institute guidelines state that a maximum of 10% undertriage is acceptable in the Netherlands [4]. The mean undertriage across all inclusive trauma regions in the Netherlands was 31.4% in 2016 [5].

The first step of the multicomponent strategy to determine the optimal receiving facility is to identify patients in need of specialized trauma care. This is performed by Emergency Medical Services (EMS) professionals on-scene and is influenced by both the pre-hospital triage protocol and the judgment of the EMS professional. The 8th version of the National Protocol of Ambulance Services (NPAS; in Dutch *Landelijk Protocol Ambulancezorg*) is currently used by all EMSs in the Netherlands as the primary pre-hospital triage protocol. A recent study reported that strict adherence to the criteria of the NPAS would have led to an undertriage rate of 63.8%, with an overtriage rate of 7.3% in one inclusive trauma region [6]. Moreover, a systematic review did not identify any pre-hospital triage protocol that by itself complied with the target of 10% undertriage [7].

The Trauma Triage App (TTApp), a smartphone and tablet application that incorporates a prediction model, was recently developed to identify patients in need of specialized trauma care. The main function of the TTApp is to predict an individual patient’s probability of being severely injured. An advice regarding whether a patient requires specialized trauma care is then generated based on a pre-defined threshold probability. This novel approach to trauma triage was externally validated retrospectively in 6859 patients from a different EMS and was able to retain a c-statistic of 0.83 with proper calibration [8]. An undertriage rate of 11.2% with a combined overtriage rate of less than 50% can hereby be achieved, depending on the threshold probability.

Notwithstanding these promising validation results, the impact of the use of the TTApp in daily practice remains to be established. The TESLA (Trauma triagE using Supervised Learning Algorithms) stepped-wedge cluster-randomized trial was designed to evaluate whether the availability of the TTApp during field triage indeed leads to a decrease in undertriage, while preserving acceptable overtriage rates.

## Methods/design

### Study design

The TESLA trial is a prospective, stepped-wedge cluster-randomized trial (SW-CRT). In a SW-CRT, clusters are randomized into allocation sequences. These sequences all start with one or more periods under the control condition, followed by the remaining periods in which the intervention is implemented. In this trial, the participating EMS regions (the clusters) will be randomized upfront to determine the period after which two paired clusters will switch to the intervention condition. Clusters within the same inclusive trauma region were paired to ease implementation in practice. Randomization of allocation sequence was completed using computer random number generator on the primary research site ([name]) prior to the recruitment of participants. Simple randomization was preferred to other techniques as the number of clusters was small and because there was no need to balance the influence of covariates. No methods to conceal the allocation sequence nor blinding was applied on either patient or cluster level. Our aim is to include 1920 consecutive severely injured patients in five steps, each with a duration of 4 months (details about the sample size below). All clusters will start with one or more steps of usual care (the NPAS). At the end of each step, two clusters will switch from the NPAS to the intervention condition (the TTApp used as an add-on to the NPAS). Key study design features are shown in Fig. 1.

**Fig. 1 Fig1:**
[figure not shown]
The stepped-wedge design of the TESLA-trial. Abbreviations: EMS, *Emergency Medical Service*; TTApp, *Trauma Triage App*

### Participating regions

Eight out of 25 EMSs (the clusters) in the Netherlands, with approximately equal patient volumes, were selected to participate in this trial (Fig. 2). A combination of EMSs with heterogeneous service areas (i.e., urban, suburban, and rural) was selected to improve the generalizability of the results. All participating EMS regions take part in the Pre-hospital Trauma Triage Research Collaborative. These EMSs are an integral part of five distinct inclusive trauma regions and cover urban, suburban, and rural areas. All 37 hospitals with a trauma-receiving emergency department within these five distinct inclusive trauma regions participate in the collection of relevant patient outcomes. All hospitals with an emergency department within these regions are designated a level of care being either one, two, or three. Level one is considered a higher-level trauma center, whereas both level two and three trauma centers are acknowledged as lower-level trauma centers.

**Fig. 2 Fig2:**
[figure not shown]
Service regions of the participating Emergency Medical Services

### Study population

All patients, 18 years of age or older, evaluated on-scene by an EMS professional, suspected of moderate to severe injuries, defined as an Injury Severity Score (ISS) ≥ 9, will be assessed for eligibility. Patients transported to a hospital outside of the participating trauma regions will be excluded. Patients that are dead on arrival at the initial receiving emergency department will also be excluded.

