### Pre-hospital trauma triage tools

#### Usual care: National Protocol of Ambulance Services

No adjustments to daily practice of EMS professionals will be introduced prior to the switch to the intervention period. Assessment of injury severity is often a two-step process consisting of the evaluation of the pre-hospital trauma triage protocol and the final judgment of the EMS professional. The 8th version of the NPAS is currently used by all participating EMSs. This protocol is a flowchart that consists of multiple criteria to identify patients in need of specialized trauma care. If a patient fulfills one of the criteria in Table 1, the EMS professional is advised to transport the patient to a higher-level trauma center. In daily practice, it is not obligatory to adhere to the protocol or to report its advice.

**Table 1 Tab1:** Higher-level trauma center criteria of the National Protocol of Ambulance Services

ABC-unstable during evaluation on-scene	
Revised trauma score < 11	
Deteriorating Glasgow Coma Scale	
Glasgow Coma Scale < 9	
Flail chest	
Amputation proximal to wrist or ankle	
Two or more fractures of the femur and/or humerus	
Penetrating injury of head, thorax, or abdomen	
Unstable pelvic fracture	
Body temperature < 32 °C	
Neurologic deficit of one or more extremities	
Anisocoria	

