### Data collection

Pre-hospital data of trauma patients is routinely collected by EMS professionals through digital run-reports. Extra variables, mainly answers to the questionnaire and usage information, will be collected by the TTApp in the intervention period. Clinical data, including all relevant patient outcomes, of all patients admitted to one of the participating hospitals will be collected through the trauma registries of each inclusive trauma region. Injury Severity Scores will be routinely calculated within 30 days after the date of injury by trained trauma registrars for all admitted patients and those who die in the emergency department. All other included patients are assumed to have minor or moderate injuries (ISS < 16). This assumption was validated for all patients discharged from the emergency department in a previous study [6]. Hospital data and pre-hospital data will be anonymized first, and then linked using a combined deterministic and probabilistic linkage scheme. This anonymized linkage approach was validated to be both highly sensitive and specific in prior research [6]. The final dataset will be accessible by [name], [name], and MP.

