This study is limited by the fact that current population values were used to determine the sample size. These values might not reflect actual event rates during the trial. Patients require an ISS ≥ 9 to be eligible for inclusion in this trial. This is based on the assumption that EMS professionals are able to differentiate between mildly injured patients and those who are severely injured, which is likely, but might not entirely resemble actual usage. This constraint was posed to limit overtriage of a clearly non-severely injured group of patients. A second limitation is the use of an exchangeability correlation structure in the analyses. Since the design of this study, methodological literature has been moving towards more complex correlation structures (e.g., discrete time decay correlation) which might be more appropriate for stepped-wedge study designs [18]. Another potential limitation of the trial is the innovativeness of the TTApp and subsequently its dissimilarity to routinely used static decision schemes. This could potentially lead to substantial nonadherence. Due to these reasons and because of the fixed length of the steps in a SW-CRT and its inextensible nature, the sample size was calculated with a conservative estimate of the expected decrease in undertriage.

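### The article describes the trial population in three ways that do not agree, and its literal inclusion rule (EMS suspicion of ISS ≥ 9) exposes the undertriage comparison to identification bias of unknown size and direction

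*Protocol article*

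**What the plan says.** Three sections of the protocol article bear on who is in the trial.

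- **Study population.** Adults "evaluated on-scene by an EMS professional, suspected of moderate to severe injuries, defined as an Injury Severity Score" of 9 or more are assessed for eligibility. The only exclusions given are transport out of the participating trauma regions and death on arrival.
- **Discussion (limitations).** "Patients require an ISS ≥ 9 to be eligible for inclusion in this trial". The stated basis is an assumption about EMS judgment: "This is based on the assumption that EMS professionals are able to differentiate between mildly injured patients and those who are severely injured", followed by the concession "which is likely, but might not entirely resemble actual usage". The purpose is also given: "This constraint was posed to limit overtriage of a clearly non-severely injured group of patients".
- **Data collection.** Registrars score ISS for admitted patients and emergency department deaths. For the rest, "All other included patients are assumed to have minor or moderate injuries", that is, ISS below 16.

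Primary outcome defines undertriage among patients with ISS ≥ 16, and Secondary analyses restricts overtriage to ISS below 16. Study design states: "No methods to conceal the allocation sequence nor blinding was applied on either patient or cluster level".

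**The concern.** A severely injured patient whose injuries EMS staff did not recognise is a central form of undertriage. If inclusion requires suspicion, that patient leaves the denominator of the endpoint meant to count such cases.

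The loss need not be equal before and after the switch. The app exists to inform the judgment of injury severity, and its introduction comes with teaching on triage and on the study protocol. Staff know which condition they are in. If the unsuspected share changes at the switch, measured undertriage changes even when no patient's destination does. The categorical time term would not remove this, because such a change follows each cluster's own switch date.

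Overtriage is exposed too, since its denominator includes unscored patients whose inclusion cannot rest on registry ISS. Keeping overtriage acceptable is part of the aim stated in the Background, and Patient safety describes the model as less specific than usual care.

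**Working it through.** **1. The plan's own figure.** Inputs from Sample size: undertriage 0.35 against 0.25, ICC 0.098 (0.028 to 0.150), 8 clusters, two switching per step, 5 periods, 48 patients per cluster per step, significance level 0.05 (taken as two-sided).

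Mean binomial variance = (0.35×0.65 + 0.25×0.75)/2 = 0.2075. Then τ² = 0.098×0.2075 = 0.02034 and s² = 0.902×0.2075/48 = 0.003899.

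The Hussey–Hughes variance is I·s²(s² + Tτ²) / [(IU − W)s² + (U² + ITU − TW − IV)τ²]. For this layout U = 20, W = 120, V = 60, so the bracketed coefficients are 40 and 120.

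Variance = 8×0.003899×0.10557 / (40×0.003899 + 120×0.02034) = 0.001269, and SE = 0.0356. Power = Φ(0.10/0.0356 − 1.96) = 0.80. At the ICC limits it is 0.795 and 0.821, in line with the stated 0.79 to 0.82. Total: 48×8×5 = 1920. The sample size reproduces and is not in question.

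**2. The sections side by side.**

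| Reading | Undertriage (ISS ≥ 16) | Overtriage (ISS < 16) |
|---|---|---|
| Suspected ISS ≥ 9 (Study population) | Unsuspected severe patients drop out | No ISS 9–15 limit; the set depends on suspicion |
| ISS ≥ 9 required, as scored (Discussion) | Every ISS ≥ 16 patient qualifies; no bias | Denominator shrinks to ISS 9–15 |
| Unscored patients kept (Data collection) | Unaffected; they are assumed below 16 | They cannot be shown to have ISS ≥ 9, so this conflicts with the row above |

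The undertriage problem belongs to the first row and the ISS 9–15 restriction to the second. They cannot both apply.

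**3. Illustration for undertriage under the suspicion rule.** The article gives no unsuspected share, so every u below is assumed. Let u be the share of severely injured patients never suspected, all taken to lower-level centers. With true undertriage p, observed undertriage = (p − u)/(1 − u).

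| u before → after | Before (p = 0.35) | After, no true effect | Spurious difference | A true −0.10 reads as |
|---|---|---|---|---|
| 10% → 10% | 0.278 | 0.278 | 0 | −0.111 |
| 5% → 2% | 0.316 | 0.337 | +0.021 | −0.081 |
| 10% → 5% | 0.278 | 0.316 | +0.038 | −0.067 |
| 10% → 0% | 0.278 | 0.350 | +0.072 | −0.028 |
| 5% → 10% | 0.316 | 0.278 | −0.038 | −0.149 |

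With SE 0.0356 held fixed, the 10% → 5% case gives power Φ(0.067/0.0356 − 1.96) = 0.47 instead of 0.80. With no true effect, a shift of 0.038 either way raises two-sided rejection from 0.05 to Φ(0.038/0.0356 − 1.96) + Φ(−0.038/0.0356 − 1.96) = 0.19.

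**4. Illustration for overtriage.** Assume a rate of 0.30, and a relative addition r of mild patients after the switch, of whom a share q goes to a level-one center. The shift is (0.30 + rq)/(1 + r) − 0.30. For r = 0.3 it runs from −0.069 (q = 0) to +0.069 (q = 0.6). It is 0 if selection does not depend on condition.

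**The case against.** The strongest reply is that suspicion may never be used as a filter. Study population says suspected patients are assessed for eligibility, while Primary outcome rests on ISS ≥ 16 alone. Study design aims at consecutive severely injured patients. Sample size counts all 1300–1400 transported per year without a discount for unsuspected cases. Data collection relies on routine run-reports linked to registries. A cohort built that way, alike in both conditions, has no differential selection. This stands: a reader might infer that the two conditions are in fact measured in differently selected patients, and the article does not establish that.

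A reader might also infer that usual care leaves EMS suspicion unrecorded, from the remark that "it is not obligatory to adhere to the protocol or to report its advice". That sentence concerns the advice of the national protocol. The professional's own suspicion is a different matter, and run-report content is not described.

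It is fair to add that the app predicts severe injury, not ISS ≥ 9, that it asks for a judgment before giving advice, and that its use is voluntary. These points make a large shift less likely but do not exclude one. The ISS restriction is also deliberate and disclosed, so an overtriage analysis in all ISS below 16 is an addition and does not correct an error.

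The conflict of wording remains. The limitation paragraph concedes the assumption about EMS judgment without saying which rule applies.

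**Conclusion.** The sections conflict and must be reconciled. Under the literal inclusion rule, the primary comparison carries a risk of identification bias whose size and direction the article does not allow anyone to determine. The shift of about 4 points for a 5-point change in the unsuspected share is an illustration only. It rests on an assumed share and on all unsuspected patients going to lower-level centers, and it is zero if the share does not change and there is no true effect. More suspicion under the app would mask a benefit. A false benefit would need less suspicion, for which the article offers no mechanism.

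It would be too strong to say that overtriage of lightly injured patients goes unmeasured. That follows only if a scored ISS ≥ 9 is enforced, and under that reading the undertriage concern disappears.

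**What to change.** 1. Define the primary population as all transported adults with registry ISS ≥ 16, regardless of EMS suspicion, by the same rule in both conditions. Leave the other exclusions as they are.
2. Define the overtriage population by one rule based on run-report or registry items recorded identically in both conditions. Report overtriage for ISS 9–15 and, as an additional analysis, for all transported adults with scored or assumed ISS below 16.
3. Tabulate included counts and case mix by condition and step.
4. Make Study population, Data collection, Secondary analyses and the limitations paragraph of the Discussion state the same rule.

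The cost is a larger overtriage dataset and some extra analysis. Run-reports and registry ISS are already collected routinely, so the change appears feasible even though about 1536 of the 1920 severely injured patients had been included by 1 December 2019.

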### Pre-hospital trauma triage tools

#### Usual care: National Protocol of Ambulance Services

No adjustments to daily practice of EMS professionals will be introduced prior to the switch to the intervention period. Assessment of injury severity is often a two-step process consisting of the evaluation of the pre-hospital trauma triage protocol and the final judgment of the EMS professional. The 8th version of the NPAS is currently used by all participating EMSs. This protocol is a flowchart that consists of multiple criteria to identify patients in need of specialized trauma care. If a patient fulfills one of the criteria in Table 1, the EMS professional is advised to transport the patient to a higher-level trauma center. In daily practice, it is not obligatory to adhere to the protocol or to report its advice.

**Table 1 Tab1:** Higher-level trauma center criteria of the National Protocol of Ambulance Services

ABC-unstable during evaluation on-scene	
Revised trauma score < 11	
Deteriorating Glasgow Coma Scale	
Glasgow Coma Scale < 9	
Flail chest	
Amputation proximal to wrist or ankle	
Two or more fractures of the femur and/or humerus	
Penetrating injury of head, thorax, or abdomen	
Unstable pelvic fracture	
Body temperature < 32 °C	
Neurologic deficit of one or more extremities	
Anisocoria	

#### Intervention: Trauma Triage App

The TTApp is a smartphone and tablet application for both Android and iOS operating systems (Fig. 3). The application is a practical and quick-to-use questionnaire consisting of six questions that collect the required predictor values of the prediction model incorporated in the TTApp (Table 2). Four additional questions are added: the judgment of the EMS professional prior to the questionnaire, the judgment of the EMS professional after the advice returned by the prediction model, the transportation destination while displaying a map with distances to nearby hospitals, and when applicable, a screen to specify reasons to bypass the preferred hospital. The incorporated prediction model calculates the probability that a patient is severely injured. An advice whether to transport a patient to a higher-level trauma center or not is generated based on a pre-defined threshold probability. This threshold determines the sensitivity and specificity of the prediction model. Filling out the questionnaire takes approximately 30–45 s and should be performed on-scene by EMS professionals.

**Fig. 3 Fig3:**
[figure not shown]
The Trauma Triage App. A sample of screens from the Trauma Triage App. Left: the generated score indicating the probability that a patient might be severely injured based on all predictors. Middle: an input field requesting the age of the patient in years. Right: an input field requesting the mechanism of injury

**Table 2 Tab2:** Variables of the prediction model incorporated in the Trauma Triage App

Age	
Systolic blood pressure	
Glasgow Coma Scale	
Penetrating injury of head, thorax, or abdomen	
Fall > 2 m or motorcycle accident > 30 km/h or entrapment in vehicle	
Suspected moderate or severe head injury	
Suspected moderate or severe thoracic injury	
Injuries in at least two anatomical regions (head/neck, face, thorax, abdomen, extremities, and/or external injuries)	

Decision-making about whether to transport a patient to a higher- or lower-level trauma center will be carried out similarly to usual care, with the exception of the availability of the TTApp prediction and recommendations linked to that prediction. Also, alike the NPAS, the TTApp is a decision-support system that can be overruled by EMS professional judgment. Implementation of the TTApp will likely lead to the transportation of more (severely) injured patients to higher-level trauma centers, thus reducing undertriage. This might lead to a slight increase in overtriage.

The TTApp will be introduced to all EMSs in a systematic manner at the end of the baseline period. A presentation will be provided to all EMS professionals which teaches the rationale behind pre-hospital triage and the study protocol. An electronic-learning will be made available that will demonstrate the use of the TTApp. The application will subsequently be made available on the proprietary devices of the participating EMS. Additional teaching sessions will be organized for teams of ambulance professionals during the intervention phase in each region.

